### Hypotheses

For study 1, it is hypothesised that Epo vs. placebo treatment will: 1) reduce HDRS-17 scores 2) increase remission rates measured with the HDRS-17 3) improve memory and executive function, reduce the perception of negative facial expressions, and improve symptoms and quality of life.

Study 2 is designed to test the hypothesis that Epo vs. placebo treatment will: 1) improve memory 2) facilitate sustained attention and reduce the perception of negative facial expressions measured, and 3) improve mood, symptoms and life quality.

### Further outcome assessments: biomarkers of potential clinical effects

fMRI is performed before and after treatment to investigate the neurophysiological underpinnings for effects of repeated Epo administration on cognitive function and mood. The second fMRI scan is scheduled 6 weeks after treatment cessation (week 14) because hematocrit levels in the two groups should be comparable at this time point [20] and thus not confound data interpretation. We will investigate whether potential memory improvement after Epo vs. placebo administration is associated with increased hippocampal engagement during picture encoding consistent with increased hippocampal BDNF and plasticity [34,38]. The neural correlates of potential improvements in executive function with Epo vs. placebo treatment will be investigated with a spatial N-back working memory test. Finally, we will investigate whether potential antidepressant effects of Epo are accompanied by reduced cognitive and neural response to fearful facial expressions in a face-processing test similar to effects seen with existing antidepressants [32]. This would point to the modulation of emotional bias as a common mechanistically important effect of compounds with diverse neurochemical signalling mechanisms. Structural T1-weighted MRI and diffusion weighted imaging (DWI) at these time points will investigate whether Epo-treatment induces structural changes in the hippocampus and influences functional brain connectivity, respectively. Arterial spin labelling (ASL) will investigate whether Epo introduces enduring changes in global and regional cerebral blood flow (after the return of haematocrit levels to baseline).

It is known that Epo increase hippocampal BDNF and nerve growth factor (NGF) and has anti-inflammatory actions, but it is unclear whether these actions are mechanistically important for potential antidepressant effects of Epo. We will therefore investigate the effect of Epo on plasma and whole blood BDNF, NGF and inflammatory markers incl. interleukin-6 (IL-6) and C-reactive protein (CRP). Given diurnal variation in peripheral BDNF, blood samples are collected at approximately the same time for all patients. For overview of timing see table 1.

Preclinical research suggests that Epo protects against diet-induced obesity and has beneficial effects on metabolic parameters [45], which may play a role in the treatment of affective disorder [46]. The study therefore investigates the effects of Epo on metabolic parameters (fasting glucose, fasting insulin, HgbA1c, HDL-cholesterol, LDL-cholesterol and TAG) in these patients through blood sampling before and during Epo vs. placebo treatment. DXA-scanning (Lunar Prodigy, GE Medical Systems Wisconsin, USA, version 8.8) is performed to assess whether Epo affects the total lipid- and lipid-free lean mass in the body. For overview of timing see table 1.

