## Methods

### Study design

The present trial has a double-blind, placebo-controlled, parallel-group design in which participants are randomised to receive weekly infusions of either Epo (Eprex; 40,000 IU; Janssen-Cilag) or saline over 8 weeks. Patients complete a broad neurocognitive test battery assessing memory, executive function and attention at baseline, after completion of treatment (week 9) and at follow-up (week 14). Mood, symptoms and quality of life are measured at baseline and weeks 5, 9 and 14 using a variety of rating scales including the Hamilton Depression Rating Scale 17 items (HDRS-17) [1], Young Mania Rating Scale (YMRS) [40], Beck Depression Inventory (BDI) [41], Massachusetts General Hospital Cognitive and Physical Functioning Questionnaire (CPFQ) [42], and the EuroQol visual analogue scale (VAS) for quality of life (EQ-5D) [43]. Patients undergo an fMRI scan at baseline and week 14. Further, plasma and whole blood BDNF and inflammatory markers will be investigated with blood tests at baseline and weeks 5, 9 and 14. Finally, we will assess metabolic parameters with blood tests at baseline and weeks 5, 9 and 14, and body fat mass by Dual energy X-ray absorptiometry (DXA) scanning at baseline and week 9. For an overview of investigations and their timing see table 1.

**Table 1 T1:** Overview of investigations

	Interventions/Assessment domains	Tests/Evaluations	Screening	Baseline & treatment start	Active treatment phase	Treatment-free follow-up period
			
				Week 1	(Week 2-8)	(Week 9-14)
**Treatment**	Investigational drug	EPO (40,000 IU)/Placebo	-	1×	7× (weekly)	-

**Efficacy**	Neurocognitive functions	Neuropsychological testing (120 min)	-	1×	-	2× (week 9,14)
		
		MRI, fMRI and cognitive tests	1×	-	-	1× (week 14)
	
	Psychopathology	Clinical Rating	-	1×	1× (week 5)	2× (week 9,14)
		
		Questionnaires	-	1×	1× (week 5)	2× (week 9,14)
	
	Quality of life questionnaires		-	1×	1× (week 5)	2× (week 9,14)
	
	DXA scan		-	1×	-	1× (week 9)

**Safety**	Physical exam		1×	1×	7× (weekly)	3× (week 9,10,14)
	
	Vital signs		1×	1×	7× (weekly)	3× (week 9,10,14)
	
	Urine pregnancy test		1×	1×	3× (week 3,5,7)	-
	
	ECG		1×	-	2× (week 3,5)	-
	
	Adverse event monitoring		-	* Continuously until week 10*		
	
	Blood analysis	Haematology	1×	1×	7× (weekly)	3× (week 9,10,14)
		
		Blood chemistry	1×	1×	7× (weekly)	3× (week 9,10,14)
		
		BDNF, inflammatory and metabolic markers	-	1×	1× (week 5)	2× (week 9,14)

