### Safety

#### Safety profile of Epo

Epo is widely used in the treatment of anaemia and generally has a good safety profile. Some potential acute side effects are transient flu-like symptoms, rash at the injection site and headache, which are normally reported as mild and disappear within a few hours. However, long-term Epo-treatment can induce epileptic seizures in medically ill patients with chronic renal failure and past history of seizures [49]. A very rare adverse effect of Epo treatment is a condition where the patient develops neutralising antibodies against Epo resulting in pure red cell aplasia (PRCA). This problem has only been observed in patients treated with subcutaneous injections and was solved in 2003 when the manufacturer changed the preparation, packaging and transport of Epo [50]. Today, Epo-antibody formation is thus an extremely rare condition observed with long-term subcutaneous Epo-treatment of patients with chronic renal failure [51].

Meta-analysis of 5243 renal failure patients in long-term Epo treatment showed a slight increase in mortality (17%; 95% C.I. 1-35%) potentially because of thrombosis at patients' arterial dialysis access site and insufficient treatment of hypertension [52]. Recently, a study of 522 stroke patients treated with Epo vs. placebo also revealed greater mortality in the Epo group, possibly because of interaction with recombinant tissue plasminogen activator (rtPA) used for thrombolysis as well as an unusual low death rate in the placebo group [53].

Weekly high-dose (40,000/48,000 IE) Epo administration to patients with neuropsychiatric disorder increases haematocrit after 5 weeks [20,21] calling for bloodlettings in about 40% of patients when values exceed 50% and 48% for men and women, respectively. However, continued Epo-treatment in the absence of any iron substitution was well tolerated and not associated with further haematocrit increase after 8 weeks of treatment [20,21].

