#### Safety parameters and monitoring

Patient safety is monitored with medical examinations, blood pressure measurements, blood tests, ECG and other safety measures at baseline and throughout the study until 2 weeks after cessation of Epo/placebo treatment. For an overview of the safety tests, their frequency and timing see table 1.

If blood tests show significantly increased haematocrit (>50% for men and >48% for women) at two consecutive measurements within a week, bloodletting(s) (450 ml each) will be performed weakly with no cessation of treatment until haematocrit values are normalised. In the case of significant increase in thrombocytes (> 400 billion/L) or drop in reticulocytes (< 1‰) 2 repeated controls will be performed in the following week. If these values remain abnormal, the patient is taken out of the study and monitored with weekly medical examinations and blood tests until the values are normalised or is hospitalised for observation.

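### HbA1c at weeks 5 and 9 is confounded by Epo's effect on red-cell turnover and should not be read as evidence of a metabolic effect

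*Protocol article*

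**What the plan says.** The biomarker section of the protocol article (Further outcome assessments) names six blood markers, HbA1c among them: "The study therefore investigates the effects of Epo on metabolic parameters (fasting glucose, fasting insulin, HgbA1c, HDL-cholesterol, LDL-cholesterol and TAG". The reason given is preclinical work suggesting that "Epo protects against diet-induced obesity and has beneficial effects on metabolic parameters".

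On timing, the Study design section states "we will assess metabolic parameters with blood tests at baseline and weeks 5, 9 and 14", and Table 1 agrees. The biomarker section describes sampling "in these patients through blood sampling before and during Epo vs. placebo treatment". Week 5 lies within the infusion period, and week 9 is one week after the last infusion.

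On red cells, the Safety profile section says that such dosing "increases haematocrit after 5 weeks [20,21] calling for bloodlettings in about 40% of patients". The monitoring section adds that, once the haematocrit limits are exceeded, "bloodletting(s) (450 ml each) will be performed weakly with no cessation of treatment until haematocrit values are normalised". Iron supplements are forbidden (Safety precautions).

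The biomarker section already treats haematocrit as a possible confounder of imaging. It places the second fMRI six weeks after treatment, when the arms should be comparable, and ties the blood-flow measurement to haematocrit having returned to baseline. It gives no similar caution for HbA1c.

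**The concern.** Glycation accumulates over the life of a red cell, so a younger cell population gives a lower HbA1c at the same glucose. Epo makes the population younger by adding new cells. Bloodletting adds to this: it removes cells of all ages, and the replacements are new. The trigger for bloodletting is a high haematocrit, so it falls mainly on the Epo arm.

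The distortion is caused by the treatment itself, so neither randomisation nor blinding removes it. The likely direction matches the benefit that the preclinical rationale suggests. An Epo-versus-saline difference in HbA1c at week 5 or 9 could therefore be reported as a metabolic effect when glucose has not changed. Diabetes is an exclusion criterion, so there is little room for a true fall, and an artefact could make up most of any difference seen.

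**Working it through.** **The plan's own figure.** The article gives no number for HbA1c. Its one power figure, 86% for each primary outcome, reproduces: 20 per arm and a standardised difference of 3/3 = 4/4 = 1 give 86.9% by the noncentral t at two-sided 5%. Nothing below affects it.

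**Inputs from the article.** Eight weekly infusions, so week 9 is about day 56 and week 14 about day 91; bloodletting of 450 ml; about 40% of patients bled; 20 per arm.

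**Assumptions not in the article.** Red-cell life L = 120 days; HbA1c 5.4% with glucose constant; glycation proportional to cell age; extra production spread evenly over T = 56 days; a relative haematocrit rise r of 5 to 20%.

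**Week 9, no bloodletting.** Mean cell age at steady state is L/2 = 60 days. The extra cells have mean age T/2 = 28 days. Hence

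relative HbA1c = (60 + 28r) / (60(1 + r)) = (1 + rT/L) / (1 + r), with T/L = 0.467.

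| r | Relative HbA1c | Fall, points | Fall if 30% of HbA1c does not depend on cell age |
|---|---|---|---|
| 5% | 0.975 | 0.14 | 0.10 |
| 10% | 0.952 | 0.26 | 0.18 |
| 15% | 0.930 | 0.38 | 0.26 |
| 20% | 0.911 | 0.48 | 0.34 |

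For example, with r = 10%: 1.0467/1.10 = 0.952, and 5.4 × (1 − 0.952) = 0.26. The last column is 0.7 times the fall.

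**Week 9, with bloodletting.** Assume 5 L blood volume, so each bloodletting removes 0.45/5 = 9% of cells of every age, and that the first falls on day 35 and any second on day 42. With r = 10%, a day-by-day version of the same model gives 5.14% without bloodletting, 5.06% after one and 5.00% after two. If 40% of Epo patients are bled once, the arm-level fall is 0.6 × 0.26 + 0.4 × 0.34 = 0.29 points. For r of 5, 15 and 20% it is 0.17, 0.41 and 0.51.

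**Chance of a significant difference with no change in glucose.** This uses a simple two-sample t-test with 20 per arm and the arm-level falls above. With an assumed SD of 0.4 points the chance is about 25%, 61%, 89% and 98% for r of 5, 10, 15 and 20%, against a nominal 5%. For SDs of 0.5 down to 0.3 it is 18 to 41% at r = 5% and 44 to 85% at r = 10%.

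**Week 14.** The extra cells are now 35 to 91 days old, mean 63. With r = 10%, HbA1c = 5.4 × (1 + 0.10 × 63/60)/1.10 = 5.42%. Counting six full weeks (42 to 98 days, mean 70) gives 5.48%. Without bloodletting there is no fall. After one bloodletting the model gives 5.30%, so with 40% bled the arm mean is 0.6 × 5.42 + 0.4 × 5.30 = 5.37%, a fall of 0.03 points.

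**Week 5.** No size is given. The article says only that haematocrit has risen after 5 weeks, so the week-9 figures cannot be carried back.

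**The case against.** The strongest reply is that little rests on HbA1c. It is one of six exploratory blood markers, alongside the DXA scan, and no decision rule uses it. Fasting glucose and fasting insulin are drawn at the same visits, so an HbA1c fall with both of those flat would be visible. A condensed article may also leave such a caveat to a fuller document. This limits the weight of the point but does not remove it. The article itself fixes the marker and its timing, and it applies the haematocrit caution to imaging and not to the marker that depends directly on red cells.

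A reader might also infer several stronger things that the article does not support:

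- **That a false metabolic benefit is built in.** The iron ban, together with Epo and bloodletting, may deplete iron, which could push HbA1c the other way. The net direction is likely, not certain. At a 5% haematocrit rise a significant artefact is also less likely than not.
- **That metabolic benefit is a trial hypothesis.** It is preclinical rationale. The Hypotheses section contains nothing metabolic, and neither do the primary, secondary or tertiary outcomes.
- **That week 14 is equally distorted.** The model shows no fall then without bloodletting, and the article expects comparable haematocrit at that visit.
- **That bloodletting selectively removes older cells.** It takes cells of all ages; the lowering comes from their replacement.

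**Conclusion.** The point holds for weeks 5 and 9. There, HbA1c is not a valid glycaemic comparison between Epo and saline, whichever way the net bias runs. The firm part is the mechanism together with the article's own statements on haematocrit, bloodletting and sampling times. The week-9 size is an illustration: it depends on the assumed haematocrit rise, cell life, production profile and baseline HbA1c, none of which the article gives. At week 14 only a small residual in bled patients is expected. The matter is confined to one exploratory marker. Lipids, fasting glucose, fasting insulin and DXA do not share this mechanism, and the main efficacy outcomes and sample size stand. It is still worth correcting, because the misreading is foreseeable and cheap to prevent.

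**What to change.** Add a statement to the biomarker section, or to the analysis plan, along these lines: HbA1c at weeks 5 and 9 will be reported descriptively by arm as confounded by red-cell turnover and will not be used as evidence of a metabolic effect of Epo; HbA1c at week 14 will be interpreted with caution in patients who were bled; the glycaemic conclusion will rest on fasting glucose and fasting insulin.

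The cost is a sentence or two. No new samples or visits are needed, and no dosing or bloodletting rule is involved. The loss is one exploratory marker as a between-arm comparison at weeks 5 and 9.

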### Sample size and power calculation

Sample size and statistical power for the two studies were calculated using nQuery Advisor 5.0 software. The primary outcome in study 1 is depression severity reflected by HDRS-17 after Epo vs. placebo treatment. The clinically relevant difference is defined as minimum 3 scores on this scale. The mean standard deviation in the two treatment groups is estimated to be 3 HDRS-17 scores and the mean scores to be 18 and 21 after Epo and placebo treatment, respectively. With these assumptions a sample of n = 40 patients (n = 20 per drug group) has a statistical power of 86% to detect a clinically relevant difference in HDRS-17 scores between the two treatment groups at an alpha level of 5% (2-sided test).

The primary outcome in study 2 is verbal memory, reflected by the RAVLT total score after Epo vs. placebo treatment. A recent study has shown that the mean RAVLT total score for patients with bipolar disorder in remission is 52.0 (while the mean score for healthy age-matched controls was 60.7) out of a maximum of 75 [47]. We estimate that a clinically relevant difference between drug groups in the change in RAVLT scores is at least 4 points (half-way to normal function). The mean standard deviation in RAVLT scores in the two treatment groups is estimated to be 4 points and the mean scores to be 56 and 52 after Epo and placebo treatment, respectively. With these assumptions a sample of n = 40 patients (n = 20 per drug group) has a statistical power of 86% to detect a clinically relevant difference in RAVLT total scores between the two treatment groups at an alpha level of 5% (2-sided test).

### Psychological tests

The key aspects of cognitive function affected in mood disorder, executive function, attention, memory and emotional processing, are assessed using an extensive battery of neurocognitive tests. The test battery includes following manual tests: RAVLT, Verbal and Semantic Fluency Tests, WAIS-III Letter Number Sequencing, Trail Making A and B, the Repeatable Battery for the Assessment of Neuropsychological Status (RBANS) digit span and coding tests, and the following computerised tests: Simple Reaction Time, Rapid Visual Information Processing, Delayed Match to Sample and Spatial Working Memory. Tests used for fMRI scanning are an N-back working memory task, a picture encoding task modified from Hariri et al [38], an emotional face processing task using fearful and happy Nimstim picture stimuli http://www.macbrain.org/resources.htm and a facial expression recognition task using Ekman and Friesen morphed stimuli sets [48].

### Equipment

The computerised neuropsychological test battery CANTAB (Cambridge Cognition Ltd.) are employed for a precise estimation of drug effects on accuracy and reaction times during the above mentioned tasks probing executive function, attention and memory. The effects of Epo on the neural basis of executive function, memory and emotion processing as well as potential structural changes are investigated using the in vivo non-invasive techniques of fMRI, structural T1 weighted MRI, DWI, and ASL-based measurements of cerebral blood flow. Imaging data will be collected using a Siemens Trio scanner operating at 3.0 T, at the Danish Research Centre for Magnetic Resonance (DRCMR), Copenhagen University Hospital, Hvidovre. fMRI data will pre-processed and analysed using FEAT (FMRIB Expert Analysis Tool) version 5.43, part of FSL (FMRIB Software Library version 3.3) http://www.fmrib.ox.ac.uk/fsl. Structural T1-weighted MRI data is analysed with FAST (FMRIB's Automated Segmentation Tool), FIRST (FMRIB's Integrated Registration and Segmentation Tool) http://www.fmrib.ox.ac.uk/fsl and FreeSurfer http://surfer.nmr.mgh.harvard.edu/. DWI data is analysed with FDT (FMRIB's Diffusion Toolbox; http://www.fmrib.ox.ac.uk/fsl/fdt/). Finally analysis of ASL data is performed with SPM software http://www.fil.ion.ucl.ac.uk/spm/software/spm8/ and FABBER http://www.fmrib.ox.ac.uk/fsl/fabber.

### Statistical analyses

Data will be collected until dropout from all randomised patients and analysed using repeated measures analysis of variance (ANOVA). Significant interactions were analysed further with simple main effect analyses. In the case of missing or invalid data, we will perform Per Protocol (PP) analyses for complete data sets and Intention to Treat (ITT) analysis. In the case of disparity between the results of these analyses, the outcome of the ITT analysis will be regarded as the result of the study. The statistical threshold for which results are considered significant if p ≤ 0.05 (2-tailed). Statistical analyses will be performed using the Statistical Package for Social Sciences (SPSS).

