#### Safety precautions

Given the above safety concerns and increased mortality in certain patient groups, the study inclusion and exclusion criteria (see 'Patients and screening') are strictly adhered to and patients' safety monitored closely throughout the study. Given the very low incidence of PRCA, our use of intravenous (vs. subcutaneous) administration and exclusion of patients with renal failure, we believe that the risk of PRCA in the current study is negligible. Nevertheless, reticulocyte counts as first indicator of PRCA will be carefully monitored (see below).

Patients are informed of all potential adverse effects before their inclusion in the study, instructed that iron supplements are strictly prohibited (since they would boost haematocrit levels) and advised to immediately contact their local emergency department if (1) they experience any potential symptoms of thrombosis or (2) their physician suspects PRCA. They are given a pocketsize plastic card with instruction about whom to contact in the event of these symptoms, their contact details, and important information to the medical doctor at the local emergency department.

It is ensured the temperature of the Epo is kept at 2-8°C at all times during transport and storage to avoid damage of the compound and potential associated adverse effects. To minimise the risk of acute allergic reactions, Epo/placebo is dissolved in 100 ml saline and administered as intravenous infusions over 15 minutes. After this, patients' well-being is monitored for at least 30 minutes by a nurse at the clinic in the case of potential transient side effects of Epo like flu symptoms, rash at the infusion site or head ache.

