### Current trial status

Patient enrolment started in September 2009 and is ongoing until September 2013. Status in October 2010 is that 21 participants have been screened, enrolled and randomised. One patient has had to drop out after week 5 because of abnormal laboratory results. So far, data sets including all clinical variables and biomarkers are complete for 18 participants.

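### Outcome collection ends at dropout, and some patients leave the study on laboratory values, so the deciding ITT analysis would rest on untestable assumptions for them, most of all in study 2

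*Protocol article*

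**What the plan says.** All references are to the protocol article.

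- **Statistical analyses.** The collection rule is "Data will be collected until dropout from all randomised patients". The analysis is a repeated measures ANOVA. With missing or invalid data, a per-protocol analysis of complete data sets and an ITT analysis are both run, and if they differ "the outcome of the ITT analysis will be regarded as the result of the study".
- **Safety parameters and monitoring.** The removal rule begins "In the case of significant increase in thrombocytes (> 400 billion/L) or drop in reticulocytes" and calls for two repeat controls. It continues: "If these values remain abnormal, the patient is taken out of the study and monitored with weekly medical examinations and blood tests". No HDRS-17 or RAVLT after removal is mentioned.
- **Safety precautions.** The reason for watching one of these values is given: "reticulocyte counts as first indicator of PRCA will be carefully monitored". PRCA is described under Safety profile of Epo as a very rare adverse effect of Epo.
- **Outcome assessments and Table 1.** Both primary outcomes are taken at week 9. Mood ratings are made at baseline and weeks 5, 9 and 14. Neuropsychological tests, including the RAVLT, are given at baseline and weeks 9 and 14 only.
- **Current trial status (October 2010).** Of 21 randomised patients, "One patient has had to drop out after week 5 because of abnormal laboratory results".

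**The concern.** The plan gives the last word to an analysis of everyone randomised, yet stops measuring some of them. Leaving treatment and leaving the study are treated as one event, so a patient taken off infusions for a laboratory reason also loses the week-9 assessment.

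Two things are at stake. The first is bias. At least one removal trigger is a value monitored because of a possible adverse effect of the study drug, so the patients lost may differ between arms and in how they would have scored. The second is that the loss is permanent. An analysis plan can choose how to handle missing values, but it cannot supply assessments that were never made.

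Repeated measures ANOVA, as commonly run, keeps only patients with complete data. Unless a further method is specified, the ITT analysis would reduce to the complete-data analysis that it is meant to overrule.

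**Working it through.** **1. The plan's own power figure.** Inputs from Sample size and power calculation: study 1 difference 3, SD 3; study 2 difference 4, SD 4; 20 per arm; two-sided 5%. Both give a standardised difference of 1. For a two-sample t-test the noncentrality is δ / (σ√(1/n₁ + 1/n₂)) = 1/√(1/20 + 1/20) = 3.16, with 38 degrees of freedom. Power is 86.9%, which agrees with the stated 86%. That figure uses the full 20 per arm; no allowance for loss is stated.

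**2. Loss so far.** 1/21 = 4.8%, exact 95% confidence interval 0.1% to 23.8%. The count is too small to fix a rate.

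**3. What is left for a patient removed after week 5 and before week 9.**

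| | Primary outcome | Values before removal | Week-9 value |
|---|---|---|---|
| Study 1 | HDRS-17 | baseline, week 5 | none |
| Study 2 | RAVLT | baseline only | none |

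In study 1 a model or imputation can use the week-5 rating. In study 2 the week-9 value would be wholly imputed, with no post-baseline RAVLT from that patient to inform it.

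**4. Effect on the estimate (illustration).** Assume that a share w of the Epo arm is removed, that these patients would score at the planned placebo mean, that retained Epo patients score at the planned Epo mean, and that no placebo patient is lost.

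Study 1: the all-randomised Epo mean is 18(1 − w) + 21w = 18 + 3w, so the difference from placebo is 21 − (18 + 3w) = 3(1 − w). Study 2, by the same steps: 4(1 − w). The completer differences stay at 3.0 and 4.0.

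| w (patients of 20) | Study 1, all randomised | Shift | Study 2, all randomised | Shift |
|---|---|---|---|---|
| 5% (1) | 2.85 | 0.15 | 3.8 | 0.2 |
| 10% (2) | 2.7 | 0.30 | 3.6 | 0.4 |
| 20% (4) | 2.4 | 0.60 | 3.2 | 0.8 |

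The standard error of the study 1 difference is 3√(2/20) = 0.95, so these shifts are 0.15/0.95 = 0.16 to 0.60/0.95 = 0.63 standard errors.

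More generally, if m of 20 Epo patients are lost and their mean would differ by D from that of the retained patients, the shift is (m/20) × D. With D = 6 in study 1 it is 0.30 points for m = 1 and 1.20 for m = 4.

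**5. Effect on power.** With loss in the Epo arm only and complete cases analysed (20 − m against 20), the formula in step 1 gives:

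| m lost | Noncentrality | df | Power |
|---|---|---|---|
| 0 | 3.16 | 38 | 86.9% |
| 1 | 3.12 | 37 | 86.0% |
| 2 | 3.08 | 36 | 85.0% |
| 4 | 2.98 | 34 | 82.5% |

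The fall is about 1 to 4 percentage points, so power is not the main issue.

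**The case against.** The strongest reply is that nothing in the article shows loss by arm. The blood change expected from Epo is a rise in haematocrit, which called for bloodletting in about 40% of patients in the earlier studies described under Safety profile of Epo. Here that rise is managed "with no cessation of treatment until haematocrit values are normalised", so it does not remove anyone. The article does not say that Epo raises thrombocytes, it calls the PRCA risk in this trial negligible, and removal requires values to stay abnormal after repeat controls. The one dropout is attributed only to abnormal laboratory results. Blood chemistry is also taken weekly, so a reader who infers that this patient fell under the thrombocyte or reticulocyte rule, or was on Epo, goes beyond the text. All of this stands: loss related to treatment is a risk, not a finding.

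A reader might also infer that no ITT result can be obtained. The documents do not support that. An estimate can be computed by imputation or a likelihood model, with the week-5 HDRS-17 to help in study 1, and the method may be set out in a fuller document not shown here. The absence of a stated method is not the point. What remains is that any such method rests on assumptions about unmeasured outcomes that the trial's data cannot check.

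Finally, the shifts in the illustration are smaller than one standard error, the 20% case is hypothetical, and patients removed after several infusions may have kept some benefit. That limits the size of the problem. It does not justify leaving obtainable primary outcomes uncollected.

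**Conclusion.** The point holds as a should-fix. The collection rule and the removal rule together lose week-9 primary outcomes for some randomised patients, and the ITT analysis that decides the result then depends on untestable assumptions about them. Study 2 is the more exposed, because a patient removed before week 9 contributes only a baseline RAVLT.

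The numerical effect is modest at the loss seen so far: 0.15 HDRS-17 points at 5% Epo-arm removal, rising to 0.60 at 20%. This assumes that removed patients would score at the placebo mean and that all loss is in the Epo arm; neither is known. Bias and unrecoverable data are the reasons to act, not power. With 80 − 21 = 59 of the planned patients still to be randomised at the reported status, a change would have reached most of the trial.

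**What to change.** Replace the rule that collection runs until dropout with one to this effect: patients who stop infusions for any reason, laboratory findings included, remain in follow-up for the scheduled HDRS-17, RAVLT and self-ratings at week 9, and at weeks 5 and 14 where still due, unless they withdraw consent; all are analysed in the arm to which they were randomised. Reserve the term dropout for withdrawal of consent.

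In Safety parameters and monitoring, reword the statement that such patients leave the study so that it agrees with this rule. The laboratory limits and the clinical stopping rule are not touched.

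The cost is protocol wording plus one or two extra assessment sessions for a few patients; Table 1 puts neuropsychological testing at 120 minutes. The weekly safety visits after removal give a point of contact, but they run only until values normalise or the patient is hospitalised. Some patients may therefore no longer be attending by week 9 and would have to be invited back, so some missing data should still be expected.
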